### Interventions

#### Intervention description {11a}

##### Trial group

The main intervention method in the trial group is Shi’s cervical manipulation therapy. The manipulation treatment team is composed of six clinicians (two in each of the three trial centers) with a minimum of 5 years’ experience in manual operation, who are good at manual spine diagnosis and treatment and have received standard operating procedures (SOP) training in this study. Each selected subject should have a 3-dimensional (3D) computed tomography (CT) reconstruction of the cervical vertebra, as well as a special physical examination of the cervical vertebra. Each subject will receive an initial diagnosis for 15–20 min after entering the group, including brief history collection, cervical static palpation (tenderness point and muscle spasm), cervical dynamic palpation (intervertebral looseness of the cervical spine), cervical sequence activity inspection, and cervical nerve reflex. Both history and examination results should be recorded in the case report form. According to the examination results, manipulation clinicians will give a comprehensive diagnostic analysis and manipulation therapy to each subject’s cervical spine. Key points of manipulation therapy operation are as follows: (1) acupoint pressing analgesia operation, according to the treatment principle of local acupoint selection and remote acupoint selection of cervical vertebra; point rubbing; and pressing operation are performed on the thumb pulp. The pressure can be light to heavy, then heavy to light, and the operation is repeated. The specific strength is to press until thumb nail color is white, while considering patient tolerance. Each acupoint is operated for 1 min. The specific acupoints are as follows: (a) local acupoints—Fengchi (International acupoint code GB20), Fengfu (International acupoint code DU16), Tianzhu (International acupoint code Bl10), Wangu (International acupoint code GB12), Dazhui (International acupoint code DU14), Jianjing (International acupoint code GB21), Jianzhongshu (International acupoint code SI15), Quepen (International acupoint code ST12), Tianzong (International acupoint code Si11), and Ashi; (b) remote acupoints—Lieque (International acupoint code LU7), Houxi (International acupoint code SI3), and Hegu (International acupoint code LI4). (2) Bone-setting manipulation operation, according to the results of palpation and 3D CT reconstruction of the patient’s cervical spine, the clinicians will give directional and fixed-point bone-setting manipulation to treat the cervical vertebrae semidislocation. The specific operation is as follows: the patient sits on the treatment chair, with the head slightly bent forward, and the manual operation physician stands at the patient’s side, with the right side as the patient’s side, for example, the manual operation physician locks his left thumb against vertebral plate between the transverse process and the spinous process of the cervical vertebra with semidislocation, and the other four fingers stick to the patient’s left head and neck, and the middle and upper part of the elbow of the right arm slightly bent on the patient’s lower jaw, according to the vertebrae semidislocation direction, the left thumb with pushing force to the vertebral plate in the opposite direction of semidislocation, while the right forearm rotates rapidly to lift and rotate the head with a direction- and size-controlled flashing force. There is a sliding motion and snapping sound from the vertebra under the left thumb. The whole manual operation treatment lasts for 20 min each time, and is done twice a week, with the longest course of treatment lasting for 12 weeks.

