
##### Control group

The main intervention method in the trial group is oral NSAIDs. Each selected subject should have a 3D CT reconstruction of the cervical vertebra, as well as a special physical examination of the cervical vertebra. The treatment team is composed of three clinicians (one in each of the three trial centers) with the qualification of clinical medical registered doctors and senior professional titles, who have received SOP training in this study. After exclusion of the contraindications of diclofenac sodium (known to be allergic to other components of diclofenac sodium, acetylsalicylic acid, ibuprofen, and Daphne, gastric and duodenal ulcer, gastrointestinal inflammatory disease, black stool, or unknown blood history), the NSAID diclofenac sodium double-release enteric-coated capsules (Difene, manufacturer Temmler Ireland. Ltd.; 75 mg, once a day, once a time, oral) is the main intervention. Each subject will receive an initial diagnosis for 15–20 min after entering the group, including brief history collection, cervical static palpation (tenderness point and muscle spasm), cervical dynamic palpation (intervertebral looseness of the cervical spine), cervical sequence activity inspection, and cervical nerve reflex. Both history and examination results should be recorded in case report form. Each subject will obtain a patient log card, which shall be kept by the patients themselves (handed over to the physician in charge of the group at the end of the test), and will be used to record name, dose, time, discomfort, combined medication, and other information about the drug taken truthfully every day. The specific drug dosage shall be specified by the physician in charge of the group according to the drug use instructions, and the maximum duration of the medication shall be 12 weeks.

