
##### Safety evaluation index

During the test, we should observe whether there are adverse reactions and adverse events, and make records. If there are adverse events, such as adverse effects on patients’ consciousness, feeling, exercise, sleep, blood pressure, pulse, heart rate, respiration, and other normal physiological indicators, cervical fracture, skin damage, spinal cord and vertebral artery injury, gastrointestinal discomfort or ulcer, bleeding, and black stool, the occurrence of adverse reactions shall be recorded in detail on the case observation form, including the time, severity, duration, and treatment measures, and correlation with experimental treatment method shall be analyzed with comprehensive consideration of complications and combined treatment. In case of adverse reactions, the clinical observation physician can decide whether to stop the trial according to the patient condition. Patients who stop treatment due to adverse reactions should be tracked and investigated, and the results should be recorded in detail.

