##### Allocation and implementation {16c}

Upon participant enrollment, the diagnostic intervention physician is responsible for asking the person in charge of each participating clinical center for the random number and corresponding group information, and then the person in charge of each participating clinical center immediately asks for the random number and corresponding group code from the “random center” by telephone, and then the person in charge of each clinical center informs the patient of the random number, corresponding group code, and intervention measures by telephone or WeChat. The intervention physician shall not disclose the above information to the subject and the symptom and sign information collection physician.

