#### Assignment of interventions: blinding

##### Blind implementation {17a}

The random grouping and intervention plan information is a blind setting for subjects and data statistical analysts. Blinding process: the blinding process is carried out in accordance with the blinding operation specifications of single-blind clinical trial drugs, and a blinding process record file is formed; the blind bottom storage adopts a 2-level blind method: the first level is the code corresponding to two treatment groups (randomly designated as a and b), and the second level is the code corresponding to each code. The two levels of blind bottom are sealed separately, each in duplicate, and stored in the Institute of Orthopedics and Traumatology by full-time personnel (not directly involved in the research work of this project).

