#### Statistical methods

##### Statistical methods for primary and secondary outcomes {20a}

Statistical results and data analysis are the responsibility of the researcher (Statistics Center) in charge of statistics and data analysis for the entire project, and the patients are divided into the following data sets according to different situations.

Full analysis set refers to the ideal set of subjects as close as possible to the intentional analysis principle (mainly including all randomized subjects). The data set is obtained after the elimination of the smallest and reasonable method among all randomized subjects. To estimate the missing value of the main variable, the last observation carried forward (LOCF) method is used to carry forward the missing part of the test data. The number of subjects in each group who evaluate efficacy at the end point is consistent with that at the beginning of the test.

Per-protocol set, all patients who meet the trial protocol, who use 80–120% of drugs, have good compliance, do not use prohibited drugs during the trial, and complete the CRF requirements.

Safety analysis set, all cases are randomly divided into groups, at least one use of study drug, or receive manual treatment, and at least one follow-up record, constitute the safety analysis population of this study. Safety population is the main population for safety evaluation in this study.

The main variables and the comprehensive efficacy analysis are the full analysis set and the compliance scheme set, respectively; the demographic and other baseline characteristics are the full analysis set; the safety evaluation is the safety set.

For continuous variables, the number of cases, mean, standard deviation, median, and minimum and maximum values will be listed; for classified variables, the form of frequency table (frequency and percentage) will be listed. Baseline is defined as the last observation data before the first treatment.

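### Patients are called blind although they are told their treatment and can see it, and a daily discomfort log is described for the control arm only, so mild adverse events are recorded differently between arms, with unknown net direction

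*Protocol article*

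**What the plan says.** **Blinding.** Blind implementation {17a} states: "The random grouping and intervention plan information is a blind setting for subjects and data statistical analysts". Allocation and implementation {16c} says that the person in charge of each center "informs the patient of the random number, corresponding group code, and intervention measures by telephone or WeChat". The same section then forbids the intervention physician to pass this information to the subject.

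**Recording.** The control-group part of {11a} says: "Each subject will obtain a patient log card, which shall be kept by the patients themselves". The card "will be used to record name, dose, time, discomfort, combined medication, and other information about the drug taken truthfully every day". The trial-group part says of recording only that "Both history and examination results should be recorded in the case report form", and a near-identical sentence stands in the control-group part. For both arms, the safety evaluation index says that "the occurrence of adverse reactions shall be recorded in detail on the case observation form". Section {11d} adds a medication form that is not restricted to one arm.

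**Use of the data.** The objective {7} hypothesizes an advantage of manipulation in efficacy, safety and satisfaction. Sections {11d} and {20c} plan a between-group comparison of adverse reactions.

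**Safety set.** Section {20a} requires randomization, at least one treatment, "and at least one follow-up record, constitute the safety analysis population of this study".

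**The concern.** Pain, disability, SF-36 and satisfaction are all patient-reported, and so are most mild adverse events. If patients know their treatment, expectation can affect every one of these measures. A report that describes the trial as participant-blind would claim a protection that the design does not have.

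Unequal recording is a second problem. A daily prompt to write down discomfort brings out minor events that patients may not mention at a visit. If one arm has the prompt and the other does not, recorded rates can differ when true rates do not. Here the prompt is described for the comparator, in a trial that expects the comparator to look less safe.

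The safety set adds a smaller issue. A patient who is treated, is harmed, and leaves before any follow-up record drops out of the safety population.

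**Working it through.** **1. Can patients be blind?** Three facts, side by side:
- {17a}: subjects are blind to grouping and intervention plan.
- {16c}: the patient is told the group code and the intervention.
- {11a}: one arm has manual treatment by a clinician, the other an oral capsule; neither a sham nor a double dummy is described.

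The second fact contradicts the first. The third would defeat patient blinding even if the second were deleted. The treating clinicians deliver the treatment, so they are unblinded too. Blinding remains possible only for data collectors and analysts. For collectors it has to be secured: {18a} says they are not to seek out the grouping, but the section on drug distribution and recovery has an observer take back drug kits at follow-up. If that person also records outcomes, the collector is not blind.

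**2. Is recording equal?** The two arm descriptions match on CT, the initial 15–20 minute diagnosis and the case report form. They differ as follows.

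| | Manipulation | Diclofenac |
|---|---|---|
| Daily patient-held log of discomfort and other medication | none described | yes |
| Case observation form for adverse reactions | yes | yes |
| Medication form under {11d} | yes | yes |
| Treatment contacts | "is done twice a week, with the longest course of treatment lasting for 12 weeks", so at most 2 × 12 = 24 sessions | drug-kit return at follow-up; no twice-weekly contact stated |
| Common assessments during treatment | 7 (after first treatment, day 3, weeks 1, 2, 4, 8, 12) | the same 7 |

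The control arm has a daily written prompt. The manipulation arm has more face-to-face contact, but nothing shown tells the manipulation clinicians to ask about discomfort at each session. Ascertainment is therefore unequal, and the text does not settle which arm records more.

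**3. How much could unequal recording matter?** The plan gives no adverse-event rate and no capture rate, so this is illustration only. Assume true risk p = 0.20 in both arms, capture 0.90 in one arm and 0.50 to 0.70 in the other, and n = 120 per arm ({14}, {15}) with two-sided α = 0.05 ({20a}).

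Recorded rate = p × capture: 0.20 × 0.90 = 0.18, against 0.20 × 0.50 = 0.10, 0.20 × 0.60 = 0.12 or 0.20 × 0.70 = 0.14.

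With p₁, p₂ the recorded rates and p̄ their mean, the chance of a significant result against the better-recorded arm is

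Φ{ [ |p₁ − p₂| − 1.96·√(2p̄(1 − p̄)/n) ] / √([p₁(1 − p₁) + p₂(1 − p₂)]/n) }.

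- 0.18 v 0.14: Φ[(0.04 − 1.96 × 0.0473)/0.0473] = Φ(−1.12) = 0.13
- 0.18 v 0.12: Φ[(0.06 − 1.96 × 0.0461)/0.0459] = Φ(−0.66) = 0.25
- 0.18 v 0.10: Φ[(0.08 − 1.96 × 0.0448)/0.0445] = Φ(−0.18) = 0.43
- Equal capture: 0.025

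The result depends on the assumed risk. At 0.90 v 0.70 capture it is 8%, 13%, 19% and 26% for true risks of 10%, 20%, 30% and 40%. The formula is symmetric: if the manipulation sessions capture more than the diary, the same probabilities describe a false result against manipulation.

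**4. Safety set.** Section {11b} promises safety data on every withdrawn subject. Section {20a} can exclude such a subject for want of a follow-up record. The two do not fit.

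**The case against.** The card reads mainly as a drug-use record: name, dose and time come first, and it is handed in at the end. No section says that its entries feed the safety comparison. The stated safety instrument is the case observation form, which is common to both arms and lists harms of manipulation as well as of the drug. Concomitant medication is also covered for both arms by {11d}. The article refers to a case report form, SOP and investigator manual that are not shown and that might give the trial arm a diary.

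Much of this stands, and it limits the conclusion. A reader might infer that the plan will make manipulation look safer through recording alone. The documents do not support that: up to 24 in-person sessions could offset or reverse the imbalance, serious events should be little affected, and the 13–43% follows entirely from assumed capture rates. What remains is that the card does list discomfort, does so daily, and is described for one arm of two otherwise parallel texts.

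A reader might also see a flat contradiction in {16b} saying center heads do not know the groups while {16c} and {18a} give them the codes. Most of it goes away if {16b} means concealment before assignment, so it needs clarification rather than correction.

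On the safety set, {11b}, the follow-up of patients who stop for adverse reactions, and the assessment right after the first treatment should make exclusions rare. The requirement still serves no purpose.

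**Conclusion.** The claim that patients are blind is wrong. It conflicts with {16c} and cannot hold for manipulation against capsules as described. This rests on the text alone and needs no assumption. Conclusions on patient-reported pain, satisfaction and safety have to be drawn as from an open-label comparison.

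Ascertainment of mild self-reported events is unequal as described. This assumes that no matching diary for the manipulation arm stands in a document not shown. The net direction and size of the bias are unknown. The illustration shows only that plausible differences in capture, at 120 per arm, can raise a one-directional error of 2.5% several-fold; it does not estimate what will happen in this trial.

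The safety-set definition is a minor defect, likely to affect few patients.

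**What to change.** 1. Rewrite {17a}: patients and treating clinicians are unblinded; claim blinding only for data collectors and analysts, and only where it is secured (for example, by separating drug-kit recovery from outcome collection). Reconcile {16c} with it, and limit the conclusions on patient-reported outcomes accordingly.
2. Give both arms the same daily diary of discomfort and medication and the same scheduled adverse-event questions. Keep drug accountability on a separate card in the control arm.
3. If enrollment is over (the trial status gives about 31 December 2020 for its completion), report all events for safety. Add a between-arm comparison of events elicited at the common visits as a sensitivity analysis for mild events. It must not replace the full comparison, because that would discard real harms recorded between visits. Section {20b}, which rules out additional analyses, needs an exception for it.
4. Define the safety set as all patients who received at least one capsule or manipulation, and drop the follow-up-record condition, in line with {11b}.
5. State in {16b}, {16c} and {18a} when center heads learn the allocation.

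The cost is one more card for 120 patients, a short common question list, one extra table, and protocol wording. No treatment rule changes.

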#### Criteria for discontinuing or modifying allocated interventions {11b}

Participants may request to leave the study or they may be withdrawn due to study-related adverse events and shedding criteria. If a subject is discontinued from study participation due to an adverse event, they will be evaluated by the study clinicians for the need of additional treatment for neck pain. Safety data will be collected on any subject who is withdrawn from the study. Participants in both study groups may receive additional treatment. Emergency treatment for patients who have severe pain and cannot tolerate manipulation therapy or cannot improve their pain within a short period of time affecting their sleep or life should be given emergency analgesic or sedative, muscle relaxant drugs, and then be rejected from the trial.

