### Rejection criteria

Patients misdiagnosed as acute subacute neck painThe subjects mistakenly included (meeting the exclusion criteria)Those who did not receive treatment strictly and used drugs according to the regulations after being selectedNo detailed treatment recordThose who disobeyed the trial plan and combined with other drugsThose who still received other related treatment that affected the evaluation of this study at the time of selection and could not stop

Those who meet 1 of the above conditions should be rejected.

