### Shedding criteria

Intolerable adverse reactions.Serious adverse reactions.The patients’ pain continued to increase, which proved that trial participation was not suitable.The patient’s health may be damaged (for example, serious complications).Those who voluntarily withdraw or miss visits in the middle.

Those who meet 1 of the above conditions should be shedding cases.

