#### Relevant concomitant care permitted or prohibited during the trial {11d}

In principle, other pain killers, muscle relaxants, and other drugs are not allowed to be used during the trial. If there is any special situation, it must be used, and the use situation needs to be truthfully recorded in the medication registration form. The patients with other diseases before enrollment will continue to maintain the original treatment after enrollment, and the medication related to pain shall be recorded in the medication record form. When the case falls off or the patient’s compliance is poor, the reasons for the fall off and poor compliance shall be entered in the case observation form in detail, and the patient’s understanding and support shall be obtained by contacting the patient as frequently as possible; the evaluation items that can be completed shall be completed, and the last treatment time shall be recorded. The case fall off, the patient’s compliance, and adverse reactions shall be statistically described and compared and evaluated between the groups.

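### Participants rejected after randomisation for emergency drugs, other drugs or non-adherence have no stated place in the full analysis set and no assured efficacy follow-up, so the primary pain comparison can be selected on outcome

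*Protocol article*

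**What the plan says.** Four parts of the protocol article bear on the point.

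- **Section {11b}.** Patients with severe pain who cannot tolerate manipulation, or whose pain does not improve quickly enough, "should be given emergency analgesic or sedative, muscle relaxant drugs, and then be rejected from the trial". Participants may request to leave, or "they may be withdrawn due to study-related adverse events and shedding criteria". On data after withdrawal the section says only this: "Safety data will be collected on any subject who is withdrawn from the study".
- **Rejection criteria.** The first two items are eligibility errors. The third to fifth arise after entry: treatment not followed as prescribed, no detailed treatment record, and use of other drugs against the plan. One item is enough: "Those who meet 1 of the above conditions should be rejected".
- **Section {11d}.** Other painkillers and muscle relaxants are disallowed in principle, but: "If there is any special situation, it must be used, and the use situation needs to be truthfully recorded in the medication registration form". Section {11b} also allows additional treatment in both groups.
- **Section {20a}.** The full analysis set is meant to follow intention-to-treat as closely as possible, with last observation carried forward (LOCF) for the main variable and the same number per group at the end point as at the start. It also says: "The data set is obtained after the elimination of the smallest and reasonable method among all randomized subjects". What may be eliminated is not defined. A separate per-protocol set already requires compliance, drug use within limits and no prohibited drugs.

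The Shedding criteria add participants whose "pain continued to increase, which proved that trial participation was not suitable", and "Those who voluntarily withdraw or miss visits in the middle".

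**The concern.** Needing emergency drugs for unrelieved pain is a failure on the very outcome the trial measures. Taking other analgesics or abandoning the allocated treatment may be one too. If these participants leave after randomisation, the arms no longer compare the groups that were randomised, and the remaining participants have been selected partly on their pain.

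Removal need not be balanced. One limb of the emergency rule can arise only under manipulation, while drug-count adherence applies to the diclofenac arm. Under section {16c} the treating physician obtains the allocation, so decisions to reject can be made knowing the arm.

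This is also a matter of conduct. If outcome visits stop at rejection, no later analysis plan can recover the scores. The planned difference is small, so a few removals could matter.

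**Working it through.** **Step 1. Disposition of a participant given emergency drugs.**

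| Question | Protocol article |
|---|---|
| Still in the trial? | No, rejected ({11b}) |
| Efficacy visits afterwards? | Not assured; {11b} secures safety data on withdrawal, and {11d} and {20c} ask for completable evaluations only for drop-outs and poor compliers |
| In the full analysis set? | Not stated; {20a} has both an undefined elimination and equal start and end numbers |
| Other drug use as such? | Recorded ({11d}), or a ground for rejection (Rejection criteria, fifth item) |

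If rejected participants are removed, the equal-numbers statement fails. If they stay, LOCF supplies their week-12 value from before rejection.

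**Step 2. Inputs.** From Sample size {14}, NRS at 12 weeks: manipulation 1.50 (SD 1.70), control 2.08 (SD 1.65), 120 per group. Planned difference: 2.08 − 1.50 = 0.58. The article gives no rejection rate and no score for rejected participants, so both are assumed below.

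**Step 3. Removal in the manipulation arm only.** Let a share p be rejected with mean score m, and let the rest average 1.50. The whole-arm mean is (1 − p)·1.50 + p·m. After removal it is 1.50. Shift = p·(m − 1.50).

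| p | m | Shift | Share of 0.58 |
|---|---|---|---|
| 3% | 5 | 0.03 × 3.5 = 0.105 | 18% |
| 5% | 6 | 0.05 × 4.5 = 0.225 | 39% |
| 10% | 7 | 0.10 × 5.5 = 0.55 | 95% |

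Of 120 participants these shares are about 4, 6 and 12 people. The shift is also the gap between the two readings of {20a}, removal and retention, if m is the value carried forward.

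**Step 4. Removal in both arms.** As an upper bound, assume normal scores and that those removed are exactly the worst. Removing the top share f lowers a mean by SD·λ, where λ = φ(z)/(1 − f) and z is the (1 − f) normal quantile. For f = 10%, λ = 0.1755/0.9 = 0.195. For f = 20%, λ = 0.2800/0.8 = 0.350.

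*No true difference (both arms 2.08, SD 1.65):*
- 10% from each arm: the reductions cancel, so the bias is 0 and the type I error stays at 5%.
- 20% manipulation, 10% control: 1.65 × (0.350 − 0.195) = 0.26 in favour of manipulation. The remaining SDs, SD·√(1 − zλ − λ²), are 1.26 (n = 96) and 1.39 (n = 108), so SE = √(1.26²/96 + 1.39²/108) = 0.186. The chance of a significant result is then about 28% instead of 5%.

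*Planned means:*
- 20% manipulation, 10% control: (2.08 − 1.65 × 0.195) − (1.50 − 1.70 × 0.350) = 1.758 − 0.905 = 0.85.
- 10% manipulation, 20% control: (2.08 − 1.65 × 0.350) − (1.50 − 1.70 × 0.195) = 1.503 − 1.169 = 0.33.

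The same rule can therefore enlarge or shrink the difference, depending on which arm loses more participants.

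**The case against.** The strongest reply is that {20a} already describes retention. It carries missing values forward, keeps end-point numbers equal to starting numbers, limits elimination to a minimum, and reserves compliance and prohibited-drug conditions for the per-protocol set. On that reading the rejection rules touch only the per-protocol set, and the shift in Step 3 is zero if the high score is carried forward. This is a reasonable reading, but the article does not state it, and rejection from the trial is a stronger phrase than exclusion from one analysis set. Retention by LOCF also leaves the follow-up problem: the value used predates rejection.

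Three stronger readings are tempting, and the text does not support them.

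- *The bias favours manipulation.* The limb on unimproved pain is not specific to an arm, and drug-adherence checks fall on controls. Direction is unknown.
- *One missed visit discards the week-12 score.* The Shedding criteria classify such participants, and {11b} says that they may be withdrawn. But {11d} and {20c} ask that feasible evaluations be completed, and LOCF can keep them in the set.
- *The safety comparison is biased too.* Section {11b} collects safety data on anyone withdrawn, and the safety set needs only one treatment and one follow-up record.

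The conflict over other drugs is also softer than it looks. Recorded use in a special situation need not count as disobeying the plan, and use can be recorded before rejection. The article still does not say which uses lead to rejection.

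**Conclusion.** The point stands in this form: the article rejects randomised participants for outcome-related events after randomisation, assures no efficacy follow-up for them, and leaves their place in the full analysis set undefined while claiming intention-to-treat and constant numbers. The primary comparison can therefore be selected on outcome or rest on stale carried-forward scores.

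The size cannot be fixed from the article. The 0.11–0.55 range rests on assumed rejection of 3–10% at NRS 5–7 in one arm only. The two-arm figures assume that exactly the worst scores are removed. They show that unequal removal could matter against 0.58; they do not predict the bias. The textual gap is certain, and the amount and direction of bias are not. It should be corrected because uncollected scores cannot be recovered at analysis.

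**What to change.** 1. Define the full analysis set as all randomised participants, by allocated group.
2. Apply the third to fifth rejection criteria and the emergency-drug rule only when forming the per-protocol set.
3. In {11b}, replace rejection from the trial with continued collection of the outcome visits already scheduled.
4. Make the main analysis use all observed NRS scores regardless of emergency or other analgesic use. Record such use as an event after randomisation, and add one sensitivity analysis that scores these participants unfavourably.
5. State that a missed visit is a missing value and does not end follow-up.
6. Reconcile the Rejection criteria, {11b} and {11d} on which uses of other drugs are permitted and recorded and which have a consequence for analysis.

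None of this alters who receives emergency treatment, or when. The cost is revised wording and follow-up at already scheduled visits for what should be a small number of participants.
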